### Adverse events

At each visit, participants will be asked about any adverse events (AEs) that have occurred during treatment. Any AEs that occur after joining the trial will be reported in detail in the participant’s medical notes and AE log, and followed up until resolution of the event. All AEs will be assessed for seriousness, causality, expectedness and severity. All serious adverse events (SAEs) will be reported to the Academic and Clinical Central Office for Research and Development (ACCORD) Research Governance (http://www.accord.ed.ac.uk) and Quality Assurance Office based at the University of Edinburgh within 24 h of becoming aware that an SAE has occurred. Known side-effects of DCA (tingling or numbness, sleepiness, confusion, heartburn, mental fogginess and nausea) will not be recorded as AEs but will be recorded on the CRF at each visit. Admittance to hospital for surgery related endometriosis/pelvic pain, exacerbation of pain related to endometriosis/pelvic pain, or elective treatments planned prior to enrolment will not be reported as SAEs.

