### Study design

This is a single site, open-label exploratory study of women with endometriosis.

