## Discussion

Dichloroacetate (DCA) may be a potential novel non-hormonal treatment for endometriosis-associated pain in women. To date, this is the first study investigating DCA for endometriosis pain and assessing whether it is possible to achieve acceptable recruitment and retention rates. Given that many trials struggle with recruitment and often request extensions or become at risk of closure [23], investigating the feasibility and acceptability of treatments or interventions is of great importance to inform design of future definitive controlled trials [24]. If there are any indicators of problems with feasibility and acceptability affecting recruitment, retention, or safety, those relevant procedures will be revised and modified.

Our sample size of 30 women and 6 months recruitment period would be reasonable to provide a justified information of feasibility, acceptability to methodology (recruitment, retention, treatment, follow-up frequency), compliance rate and response to questionnaires. A key strength of the study is the clear definition of participant’s disease as endometriosis diagnosed via laparoscopy within the past five years (excluding deep endometriosis), and the specific inclusion and exclusion criteria would be reflective to the patient’s eligible to be on DCA in the future RCT based on their suitability for DCA as treatment option.

The questionnaires used to measure the physical and emotional functioning were selected based on the Initiative on Methods, Measurement, and Pain Assessment in Clinical Trials (IMMPACT) recommendations for chronic pain trials which would provide a reflective account on the women’s experiences [15–18]. Although pain scores and satisfaction rates are being used as part of the study protocol, the trial is not designed nor powered for formal analysis of effectiveness. The questionnaire results (e.g. pain score, physical and emotional functioning) from this study will not be carried forward for future studies. However, the nature and number of unanswered questions in the questionnaire can help us to assess suitability of the questionnaires and identify important outcome measures for future study.

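### Unplanned admissions for worsening endometriosis or pelvic pain are exempt from SAE reporting whatever the causality assessment says, so one judged possibly related to DCA has no stated 24 h report

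*Protocol article*

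**What the plan says.** All of the reporting rules are in the Adverse events section of the protocol article.

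- **Recording.** Any AE after joining the trial is entered in the participant's "medical notes and AE log, and followed up until resolution of the event".
- **Assessment.** "All AEs will be assessed for seriousness, causality, expectedness and severity".
- **Expedited reporting.** Every SAE goes to the ACCORD research governance and quality assurance office "within 24 h of becoming aware that an SAE has occurred".
- **Exemption.** Three reasons for admission are then removed from SAE reporting. The first is "Admittance to hospital for surgery related endometriosis/pelvic pain". The second and third are in the rest of the sentence: "exacerbation of pain related to endometriosis/pelvic pain, or elective treatments planned prior to enrolment will not be reported as SAEs".

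Three other statements bear on the point. Study design: "This is a single site, open-label exploratory study of women with endometriosis" (the title adds that it is single-arm). The Discussion says that "this is the first study investigating DCA for endometriosis pain", and that "the trial is not designed nor powered for formal analysis of effectiveness". How well DCA is tolerated is a listed secondary outcome.

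**The concern.** An exemption for treatment arranged before enrolment is sound, because DCA cannot have caused the need for it. The pain-exacerbation limb is different in kind: such an admission arises during the study and is not planned. The exemption is set by why the woman was admitted and has no exception for an event that the investigator thinks DCA may have caused. Causality is assessed, but the answer does not change whether the event is reported.

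In many trials, setting aside admissions for the underlying disease is a reasonable way to reduce noise. It is less comfortable here. The underlying symptom is the one the drug is meant to treat, and DCA has not been studied for it before. There is no comparator against which a rise in pain admissions would stand out, and pain is not formally analysed for effectiveness. At stake are a prompt report outside the investigator's team of a possible drug-related worsening, and an SAE count that can be read at face value when the results are used to design the future RCT.

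**Working it through.** No arithmetic applies. The article states no admission rate or expected SAE count, and the point depends on none. The check is a reading of the exemption against the rules around it.

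**Step 1: which limbs does prior planning qualify?**

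| Reason for admission | Limited to admissions planned before enrolment? | Reported as SAE? |
|---|---|---|
| Surgery related to endometriosis or pelvic pain | Ambiguous. The natural reading is no, because the planning words follow the third item, but they could be read back to surgery | No |
| Exacerbation of endometriosis or pelvic pain | No. An exacerbation cannot sensibly be planned | No |
| Elective treatment | Yes, stated | No |

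The second row is secure on any reading. The first is probable but not certain.

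**Step 2: follow one event through the rules.** Suppose a woman on DCA has an unplanned admission for worsening pelvic pain, and the investigator judges it possibly related to DCA.

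1. It occurred after she joined the trial, so it goes into the medical notes and AE log and is followed to resolution.
2. It is assessed for seriousness, causality, expectedness and severity. The article does not define seriousness. The exemption would be unnecessary, however, unless an admission could otherwise count as an SAE.
3. The reason for admission matches the second limb, so the event is not reported as an SAE. The sentence does not refer back to the causality result in item 2.
4. The 24 h rule applies to SAEs. No other expedited route is described for this event.

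The same event judged unrelated to DCA ends in the same place. The causality assessment is made but does not affect reporting.

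**Step 3: what is kept and what is lost?** The same section handles the known side-effects of DCA differently: those are kept off the AE record and noted on the CRF. Nothing similar is said of pain admissions, so they remain AEs. What is lost is the 24 h report and the place in the SAE count.

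**Step 4: is there a link to dose?** Under Intervention (option 1), a woman who still has pain at the end of week 6, with minimal or no side-effects, is asked to increase her dose. Persisting pain and the higher dose therefore go together by design. An exempt admission is hard to interpret later unless the dose at onset was recorded with it.

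**The case against.** The case on the other side has real weight, and much of it stands.

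- **The events are not lost.** A reader might infer that these admissions vanish from the safety record. They do not: log entry, assessment and follow-up all continue. A medical doctor examines each participant at every visit, and a medical doctor oversees dose escalation. Worsening would be seen locally, so SAE reporting is not the main means of detecting it. It is the only expedited route that the article describes.
- **There is no internal contradiction.** A reader might set the rule that all SAEs are reported against the exemption and call them inconsistent. A general rule followed by a named exception in the same paragraph is ordinary drafting. The criticism is of the exception's scope.
- **Other causes of acute pelvic pain.** A reader might infer that these escape reporting too, because the exemption names pelvic pain as well as endometriosis. The text does not establish this. A separately diagnosed condition can be reported as its own event under the general rule.
- **Death or life-threatening events.** The sentence lists reasons for hospital admission. It does not say that a fatal or life-threatening event is exempt.
- **Deliberate choice and condensed article.** Exempting disease-related admissions can be intended, and the full protocol may qualify the rule. That is possible, but the article states the exemption without qualification, and the point is about what it states.

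None of this answers the narrow point: for an unplanned exacerbation admission judged possibly related to DCA, the rule as written gives no 24 h report.

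**Conclusion.** The point holds in a limited form and is worth a cheap correction. As written, an unplanned admission for exacerbated endometriosis or pelvic pain is outside SAE reporting even if the investigator attributes it to DCA. On the natural though ambiguous reading, the same is true of unplanned related surgery. The consequence is a missing 24 h report to the ACCORD office and a missing entry in the SAE count, not a missing record.

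The size cannot be put in figures. With 30 women planned and no admission rate in the document, any count would be invented. It may be tempting to infer from the entry requirement of an average pain score of at least 4 that such admissions will be common, but that score says nothing about how often women are admitted.

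The conclusion rests on two assumptions: that the exemption is applied as the article words it, and that an unplanned admission would otherwise be an SAE, which the existence of the exemption implies. Whether every disease-related admission should be reported as an SAE is open to debate, and the conclusion does not require it. It requires only that the causality assessment should affect reporting.

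**What to change.** In the Adverse events section:

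1. Keep the full exemption only for admissions and procedures planned before enrolment, and word it so that this limit clearly covers surgery.
2. For unplanned admissions for pelvic-pain exacerbation or related surgery, record the event on the AE log as serious, with the dose of DCA at onset. Causality assessment is already required.
3. Report to the ACCORD office within 24 h any such admission judged possibly related to DCA.
4. Tabulate all such admissions in the tolerability results, whether or not judged related, so that a reader of the SAE count can see what was set aside.

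If the full protocol already says this, the article's sentence needs only the matching qualifier. The cost is a change of wording and a few extra forms in a 30-woman study. Nothing in treatment, visits or sample size changes.

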### Termination of study

All participants will be required to stop DCA treatment after 12 weeks and return any remaining DCA to the investigator at the end of the study. Participants may withdraw from the trial at any point or a participant can be withdrawn by the investigator. Although pregnancy is not considered an adverse event, any participant’s pregnancy will be recorded on a Pregnancy Notification Form and submitted to the ACCORD office within 14 days of being made aware of the pregnancy. All pregnant participants will be followed up until the outcome of the pregnancy. Data collection is envisaged to be completed in August 2020.

### Sample size

The emphasis in this study is to establish feasibility, not statistical significance. This study is designed primarily to explore the effectiveness of the proposed field methodology: recruitment, retention, study processes and compliance with treatment. We will aim to recruit as many women as possible over a 6-month period. We estimate that we will recruit 5–6 patients per month and will aim to recruit 30 patients. Data from this exploratory study will be used to refine sample size calculations for any future RCT.

### Statistical analysis

Summary data will be used to describe baseline characteristics: mean and standard deviation, or median and interquartile range (IQR), and minimum, maximum for continuous variables and number (percentage) of individuals for categorical variables. Since this is a single-arm trial with no randomisation, there is no risk of patients not receiving their randomised treatment. However, patients will be assumed to have completed the treatment as prescribed in the primary analysis, unless they failed to start treatment.

### Primary endpoint

The primary endpoint is to determine recruitment and retention rates. Using the information collected from the participant log, we will determine the number of patients recruited from the pool of eligible women and a 50% of 60, 95% CI (36.8–63.2%) recruitment will be deemed acceptable. While a retention rate of 100% would be ideal, we will consider a rate of 80% satisfactory. We will provide an estimate of the proportion and its 95% CI (61.4–92.3%). In addition, we will determine the nature and number of unanswered questions in each questionnaire. We aim to determine whether the trial design will perform well enough in the field to warrant rolling out the study to full trial. All analysis will be carried out in the University of Edinburgh.

### Secondary endpoints

Acceptability of proposed methods of recruitment, follow-up, treatments and questionnaires used in this study will be assessed quantitatively using self-reported side-effects and acceptability questionnaires at the end of study. We also aim to determine if treatment is acceptable in terms of self-reported compliance (from treatment diaries). The blood samples collected from patients will be analysed at University of Edinburgh, QMRI, to detect the systemic levels of DCA to confirm participants’ compliance. The assay will be developed in the research laboratory of the Edinburgh Clinical Research Facility. It will be analysed using mass spectrometry (choosing the instrument that will provide most accurate readings) and either Analyst MultiQuant software or Xcalibur Quantitate software. Descriptive statistics will be used to describe use of rescue analgesia, side-effects and compliance and will be compared by dose escalation or not.

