### Intervention

Based on our current preclinical studies and the current literature, we have chosen a dose which will potentially be effective for endometriosis-associated pain and has the least side-effects. Trials using DCA as a potential treatment for cancer or pulmonary arterial hypertension suggest that doses of 6.25 mg/kg BD should produce blood levels within the range required for pyruvate dehydrogenase kinase (PDK) inhibition, although DCA pharmacokinetics may be variable [15]. We also note that most side-effects, such as reversible peripheral neuropathy, seem to occur at doses of 25–50 mg/kg/day [16–18]. We therefore plan to trial the feasibility of a dose change with DCA at approximately 6.25 mg/kg BD (oral) for 6 weeks, followed by a dose increase to approximately 12.5 mg/kg BD (oral) for the next 6 weeks, depending on participant’s tolerance of treatment (total treatment phase of 12 weeks).

The drug will be provided in capsules containing 333 mg or 500 mg of DCA powder (Curaltus Ltd, Lithuania). Participants will be required to take between two to six capsules orally a day depending on the dose calculated using their body weight. The drug will be dispensed on day 1 of treatment and resupplied if needed at each visit during week 2, 6 and 8. Sufficient amount of drug will be provided to last until the next visit or end of study.
*Weeks 1–6*. All participants will receive approximately 6.25 mg/kg BD daily (oral) for 6 weeks.*Weeks 6–12*. Dosing may be escalated depending on symptom control and side-effects (options 1–3 as below).
*Option 1*. If the participant still has painful symptoms at the end of week 6 and minimal or no side-effects, she will be asked to increase the dose of DCA to approximately 12.5 mg/kg BD daily (oral) for a further 6 weeks (see Figure 1, study flow chart). Dose escalation will be overseen by a medical doctor on the delegation log.*Option 2*. If DCA has been helpful in reducing painful symptoms and caused minimal side-effects, then the participant will be asked to continue to take DCA 6.25 mg/kg BD daily (oral) for a further 6 weeks.*Option 3*. If the participant suffers from side-effects from DCA and the dose of DCA taken does not provide relief for endometriosis pain, the participant is allowed to stop taking the drug at any stage of the treatment, but they will continue to be followed up with their consent.

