**Fig. 1 Fig1:**
[figure not shown]
Study Flow chart. DCA, Dichloroacetate. NRS, Numerical Rating Scale

If participants who take 12.5 mg/kg BD (oral) have side-effects and do not tolerate the treatment, they will be allowed to return to low dose of 6.25 mg/kg BD. If participants do not have enough capsules to return to low dose, they will be resupplied with new capsules.

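### Comparing side-effects, rescue analgesia and compliance by escalation status compares groups selected on those outcomes, so the contrast cannot be read as a comparison of doses

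*Protocol article*

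**What the plan says.** The planned analysis (Protocol article, Secondary endpoints) is: "Descriptive statistics will be used to describe use of rescue analgesia, side-effects and compliance and will be compared by dose escalation or not". No period, adjustment or caution goes with it.

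The grouping is set under Intervention, where the general rule is "Dosing may be escalated depending on symptom control and side-effects". Three options follow:

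- Option 1 (escalate): "If the participant still has painful symptoms at the end of week 6 and minimal or no side-effects".
- Option 2 (stay on the lower dose): "If DCA has been helpful in reducing painful symptoms and caused minimal side-effects".
- Option 3 (may stop the drug, at any stage): "If the participant suffers from side-effects from DCA and the dose of DCA taken does not provide relief for endometriosis pain". Of these women the article says "they will continue to be followed up with their consent".

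The text below Fig. 1 adds that women who do not tolerate the higher dose may step down: "they will be allowed to return to low dose of 6.25 mg/kg BD". The Statistical analysis section confirms that nothing is allocated by chance: "Since this is a single-arm trial with no randomisation".

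**The concern.** Escalation is decided at week 6 from pain and side-effects. Two of the three quantities to be compared are side-effects and analgesic use, so the grouping variable is partly a function of the outcomes.

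- **Side-effects.** Option 3 women, and women with relief but more than minimal side-effects (who fit none of the three options), are not escalated at week 6. Their week 1–6 intolerance is counted in the non-escalated group, although every woman was on the lower dose in that period.
- **Rescue analgesia.** Escalated women are chosen because they still hurt. More analgesic use among them is expected whatever the dose does.
- **Compliance.** Option 3 women may stop the drug, which can lower compliance in the non-escalated group for a reason unrelated to dose acceptability.
- **Label.** Because step-down is allowed, having been escalated is not the same as being on the higher dose.

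Tolerability of DCA is a listed secondary outcome, and the Intervention section says the trial is to test the feasibility of a dose change. The higher dose is 2 × 12.5 = 25 mg/kg/day, the lower end of the 25–50 mg/kg/day range in which the same section says most side-effects seem to occur. The Adverse events section records known side-effects on the CRF and not as adverse events, so this comparison is the only dose-related analysis of them that the article describes. A contrast that is too favourable, or reversed, would mislead at that point.

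**Working it through.** **Plan's own figure.** None is given for this comparison, and the article states no side-effect or relief rates. All rates below are assumptions, used to show direction and range.

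**1. Cumulative 12-week count, no correlation within women.**

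Assumed: s = 0.30, the probability of a more-than-minimal side-effect in each six-week period; r = 0.40, the probability of adequate relief at week 6; relief independent of side-effects; later risk independent of history. Escalation as in Option 1.

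- Escalated: (1 − s)(1 − r) = 0.70 × 0.60 = 0.42, about 13 of 30 women. Not escalated: 0.58, about 17 of 30.
- Side-effect in weeks 1–6 among the non-escalated: 0.30 / 0.58 = 0.517. Among the escalated: 0 by selection.
- Over 12 weeks, non-escalated: 0.517 + 0.483 × 0.30 = 0.662.
- Over 12 weeks, escalated: 0.30 with no dose effect; 0.60 if the higher dose doubles the later risk.

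So the table would show **30% v 66%** when dose does nothing and **60% v 66%** when the later risk doubles.

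Range with no dose effect, from s / (1 − (1 − s)(1 − r)) and then adding later events:

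| s | r | escalated | non-escalated |
|---|---|---|---|
| 0.10 | 0.30 | 10% | 34% |
| 0.10 | 0.50 | 10% | 26% |
| 0.40 | 0.30 | 40% | 81% |
| 0.40 | 0.50 | 40% | 74% |

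**2. Same assumptions, weeks 6–12 only.** The later risk does not depend on history, so the result is 30% v 30% with no dose effect and 60% v 30% if the risk doubles. There is no bias in this window.

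**3. Weeks 6–12, side-effects correlated within women.** Let each woman's risk follow a beta distribution with mean m = 0.30 and correlation ρ between periods, with pain persisting in half of women. Then 0.70 × 0.50 = 0.35 escalate. With no dose effect, the escalated risk is m(1 − ρ) and the non-escalated risk is (m − 0.35 × m(1 − ρ)) / 0.65. At ρ = 0.5:

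- escalated 0.30 × 0.5 = 0.15;
- non-escalated (0.30 − 0.35 × 0.15) / 0.65 = 0.381.

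Simulation gives the results when the higher dose doubles the odds of a side-effect (a smaller effect than doubling the risk):

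| ρ | true risk, higher v lower dose | weeks 6–12, escalated v non-escalated | 12 weeks, escalated v non-escalated |
|---|---|---|---|
| about 0 | 46% v 30% | 46% v 30% | 46% v 62% |
| 0.2 | 43% v 30% | 36% v 33% | 36% v 59% |
| 0.5 | 38% v 30% | 22% v 38% | 22% v 54% |

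With m from 0.2 to 0.4 and persisting pain in 50–70%, the weeks 6–12 gap is close to nil at ρ = 0.2. It is reversed throughout at ρ = 0.5 to 0.7, for example 15% v 27% (m = 0.2, ρ = 0.5) and 17% v 60% (m = 0.4, ρ = 0.7).

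**4. Where the imbalance comes from.** Option 2 also requires minimal side-effects. Set against Option 2 women alone (m = 0.30, ρ = 0.5, doubled odds, half with persisting pain), the escalated show 22% v 15%. The direction is right, though both figures lie below the all-women risks of 38% and 30%. The side-effect imbalance therefore comes from Option 3 and the unclassified women.

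**The case against.** The strongest reply is that this is one descriptive sentence about secondary data in about 30 women. The primary endpoint is recruitment and retention, the Sample size section puts feasibility ahead of statistical significance, and no test depends on the comparison. That stands, and it limits the severity. It does not remove the problem: selection affects a descriptive table as much as a test. The Discussion's caveat concerns effectiveness and does not mention this contrast.

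Second, the large figures need a cumulative count. The article names no window, and known side-effects are recorded at each visit, so a weeks 6–12 table fits the text equally well. This also stands. A reader might infer that the comparison is sure to hide or reverse harm; the article does not support that. The calculation has two further limits. It gives escalated women no week 1–6 events, whereas they may have had minimal ones, and counting those would narrow the gap. It also leaves non-escalated women at the lower-dose risk even if they have stopped; stopping would lower their weeks 6–12 rate and pull the other way.

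Third, a reader might infer that a wrong dose would be carried into the future RCT. No section says the RCT dose will be chosen from this table. The stated uses are field methodology, sample-size refinement, the recruitment time frame, and revising procedures if feasibility, acceptability or safety problems appear.

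Fourth, a reader might assume that everyone who stops is non-escalated. Option 3 allows stopping at any stage, so women who escalate and then stop would be in the escalated group.

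Finally, the counting window and the classification of step-downs may be settled in the full protocol or SAP. Their absence from an article is not itself a fault. The grouping is stated, however, and the grouping is what is wrong.

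**Conclusion.** The point holds at moderate severity. The comparison by escalation status is between groups selected on pain and side-effects, so it cannot be read as lower against higher dose for any of the three outcomes, and the article gives no warning of this. For side-effects it can make the higher dose look better tolerated. For rescue analgesia the likely bias is in the opposite direction.

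The size is conditional. On assumed rates of 30% side-effects per period and 40% relief, a 12-week count shows 30% v 66% with no dose effect. Across side-effect rates of 10–40% and relief of 30–50%, it runs from 10% v 26–34% to 40% v 74–81%. In a weeks 6–12 count the model shows bias only with within-woman correlation: almost no gap remains at ρ = 0.2 when the odds are truly doubled, and the sign reverses at 0.5 and above. Recruitment and retention are unaffected.

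**What to change.** Replace the sentence under Secondary endpoints with four statements:

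1. Side-effects, rescue analgesia and compliance in weeks 1–6 are tabulated for all women together, since all start on the lower dose.
2. Weeks 6–12 are tabulated by visit interval and by dose actually taken (lower, higher, stepped down, stopped), with Options 1, 2 and 3 shown separately and women who fit no option identified.
3. For escalated women, the within-woman change from weeks 1–6 to weeks 6–12 is shown.
4. Escalated and non-escalated women are selected on week-6 outcomes and are not compared as dose groups.

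Visit intervals suit the data better than event rates per week of exposure: known side-effects are described as recorded at visits, with no mention of onset dates. Item 2 needs the dose taken in each interval to be recorded. The article describes a treatment diary and CRF compliance entries but no explicit dose history, so this should be confirmed.

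The cost is somewhat more tabulation and small cells: on the assumptions above, about 13 escalated and 17 non-escalated women before further splitting. The dosing rule, visits and primary endpoint need no change.
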